## **PROJECT DESCRIPTION**

**TITLE: Efficacy and safety of increased dosage of Praziquantel (60mg/Kg) in the treatment of schistosomiasis**

**PI: [name]**

### **1. INTRODUCTION**

Schistosomiasis is currently estimated to infect about 200 million people World-wide, and 85% of them are believed to be in sub-Saharan Africa. It is ranked second to malaria in terms of extent of endemic areas and number of infected people. Several control options have been previously advocated, however, our better understanding of the epidemiology of the infection and disease, the advent of safe, efficacious, single oral dose anti-schistosomal drugs point to the strategy of morbidity reduction by chemotherapy as the mainstay of schistosomiasis morbidity control (WHO, 2002). Praziquantel (PZQ) is currently a drug of choice for the treatment of schistosomiasis because of its high effectiveness against the adult stage of all human schistosomiasis species, its ease of administering (single oral dose) and its good safety profile with usually mild adverse side effects (Kumar, et al, 1994). Moreover, the price of PZQ has recently been substantially reduced (WHO, 2002) making it more available and affordable for most people in endemic countries.

Praziquantel is an isoquinoline-pyrazine derivative (2-cyclohexylcarbonyl-1,3,4,6,7,11b-hexahydro-2H-pyrazino (2,1-a)isoquinoline-4-one). It has a broad antiparasitic effect and first marketed as a veterinary taeniocide under the trade name Droncit (Bayer) (MacMahon & Kolstrup (1979). Clinical studies in man have shown that it is effective in human tapeworm infestation and all human schistosome infections. The recommended dosage of PZQ is 40mg/kg body weight given orally as a single dose (WHO, 1993), although higher doses of up to 75mg/kg have been given and found to be rapidly absorbed, metabolized and well tolerated. The mere fact that PZQ is given as a single dose improves compliance compared to earlier products (antischistosomal drugs such as amblihar and metrifonate) which required multiple administrations lasting over several days or weeks.

In Tanzania PZQ at 40mg/kg body weight as a single dose has been tested against infections by *S haematobium* (McMahon & Kolstrup, 1979) and *S mansoni* (Rugemalila et al., 1984). McMahon & Kolstrup (1979) recorded high cure rates of 83%, 76% and 71% against *S haematobium* at 1- month, 2- months and 6- months, respectively. In *S mansoni*, however, Rugemalila et al. (1984) observed lower cure rates of 35%, 56% and 63% at 1-month, 2- months and 6- months, respectively.

The unusually low cure rates reported by Stelma et al. (1995) in Senegal, while working in very intense focus of *S. mansoni*, has raised much concern about the emergency of resistance or tolerance of schistosomes to PZQ. So in order to circumvent this problem, several strategies to reduce the rate of schistosome species developing resistance against PZQ and to optimize the use of PZQ in schistosomiasis control has been suggested. In the present study, the suggested option to be explored is to increase the dose regimens of PZQ up to 60mg/kg body weight.

Stelma et al. (1997) increased the dose of PZQ from standard dosage of 40mg/kg to 60mg/kg and showed to have no significant improvement in efficacy. Van Lieshutt et al. (1994), however, showed that the opposite was true. This controversy requires to be urgently resolved by collecting data on the safety, efficacy and effectiveness of increased doses of PZQ in different epidemiological setting where schistosomiasis is highly endemic.

Children are especially vulnerable to schistosomiasis, and infected school-age children are often physically and intellectually compromised by concurrent anemia, attention deficits, learning disabilities, school absenteeism and higher dropout rates (Guyatt et al., 2001; WHO, 2002). Schistosomiasis Control Programs target school-aged children, aiming for clinical cure and morbidity reduction. Many previous trials were done with children and adolescents to test the efficacy of praziquantel alone or in combination with other drugs (Jaoko et al., 1996; Guisse et al., 1997; Olds et al., 1999; Urtzinger et al., 2000; de Clercq et al., 2002). Since praziquantel is a safe and well known drug (as described above) and the improvement of treatment should be achieved for those who need the most, children and adolescents will be the chosen study population for this trial.

## **2. OBJECTIVES**

The main objective of this study is to determine if higher dose of praziquantel at 60 mg/kg will improve treatment efficacy with an adequate safety profile, in comparison with standard regimen of praziquantel at 40mg/kg.

### **Specifically:**

- 2.1 To determine cure rate in increased dosage regimen of PZQ 60 mg/kg in comparison with a standard dosage of 40mg/kg of PZQ in the treatment of *S. mansoni*
- 2.2 To determine egg reduction rate in increased dosage regimen of PZQ 60 mg/kg in comparison with a standard dosage of 40mg/kg of PZQ in the treatment of *S. mansoni*
- 2.3 To determine adverse reactions (events) in increased dosage regimen of PZQ 60 mg/kg in comparison with a standard dosage of 40mg/kg of PZQ in the treatment of *S. mansoni*
- 2.4 To determine morbidity (haemoglobin, weight) in increased dosage regimen of PZQ 60 mg/kg in comparison with a standard dosage of 40mg/kg of PZQ in the treatment of *S. mansoni*

## **3. EXPERIMENTAL DESIGN AND METHODS**

The trial described below will be conducted in compliance with the protocol, Good Clinical Practice and applicable regulatory requirements.

3.1. *Study site.* The study is to be done in Mwanza Region, Tanzania, where both *S. mansoni* and *S. haematobium* are highly endemic particularly in Magu and Misungwi districts. In a recent survey of schoolchildren by [name], *et al* (1999) in the area the prevalence of urinary schistosomiasis was found to be 56.5% (range 13.6-87.7%) and 10.9 % (range 0.0-64.4%) for intestinal schistosomiasis. *S. mansoni* is more prevalent along the Lake Victoria shore, while *S. haematobium* is more prevalent in the hinterland, away from the lakeshore. In this area mixed *S. haematobium/ S. mansoni* infections have a low prevalence of 4.0 % (range 0.0 – 21.0 %). The study will be done in schools reported by [name] *et al.* (1999) to have high prevalence of *S. mansoni*, i.e., Mayega 64.7%, Kigangama 53.3%, Lutale 49.5%, Kongolo 41.7%, Chumve 41.5%, Kabita 39.8%, Ihale 38.0% and Ilumwa 34.4%. Also schools located in the same area as the high prevalence schools may be considered for baseline screening. [name] (1988) have shown that peak transmission of *S. haematobium* in the area occurs during the short dry period, sometime in February/March so that most of the infections in the community would be detected in April/May. Magendantz (1972) showed that the transmission of *S. mansoni* occurs mainly in Lake Victoria throughout the year.

3.2. *Study design.* The proposed study is a double-blind, randomized controlled trial to determine if higher doses of praziquantel (PZQ 60mg/kg) will improve treatment efficacy of *S. mansoni* with an adequate safety profile, in comparison with standard regimen of PZQ 40mg/kg. The trial is to be conducted with schoolchildren aged between 10 to 19 years old. This age group is chosen because it is

school age children who are heavily infected by schistosomes, therefore, it is the group in which the new increased dosage of PZQ is anticipated to be used. The potential beneficiary of increased efficacy of PZQ is school-age children and, therefore, it would be prudent to determine the safety profile of the new dosage regimen in the same age group.

The following are the study endpoints:

- Primary endpoint:  
Cure rate at 21 days after treatment for the PZQ 60mg/Kg and PZQ 40mg/Kg groups.
- Secondary endpoints:
  - a) Egg reduction rate at 21 days after treatment for the PZQ 60mg/Kg and PZQ 40mg/Kg groups.
  - b) Comparison of frequency and severity of adverse events during the 4 hours after treatment, 24 hours and 21 days, for the PZQ 60mg/Kg and PZQ 40mg/Kg groups.
  - c) Comparison of the variation of hemoglobin (Hb) level at 21 days, 6 months and 12 months after treatment (as related to the baseline measurement), for the PZQ 60mg/Kg and PZQ 40mg/Kg groups.
  - d) Comparison of the variation of weight at 6 months and 12 months after treatment (as related to the baseline measurement), for the PZQ 60mg/Kg and PZQ 40mg/Kg groups.

The flow-chart below illustrates the study design:

[figure not shown]

Rapport with government and community leaders at district, ward, village and school levels will be established in the study area. Informed Consent will be obtained for each participant. For children considered minors written Informed Consent will be obtained from their guardians. Schoolchildren meeting the screening criteria will be recruited continuously, subjects will be examined quantitatively for *S mansoni* ova and semi-quantitatively for *S haematobium*. Two stool samples (2 Kato Katz slides will be prepared from each sample) and one urine sample will be collected within 5 days. Those who fulfill the inclusion and exclusion criteria for enrolment in the trial will be randomized to receive treatment with PZQ within 7 days (+/-1 day).

See Appendix 1 for the schedule of activities. It is estimated that 800 school children will be examined during the baseline study within one month. It is expected that about 240 children (30%) will fulfill the criteria for enrollment in the trial. Participants with positive *Schistosoma spp.* diagnosis who do not fulfill the inclusion and exclusion criteria will be treated with the standard treatment of a single dose of PZQ 40mg/Kg.

Schoolchildren in the treatment groups will be followed up for a total of 12 months post-treatment.

The following baseline screening and follow up visits will be done. As shown in Appendix 1 the baseline study is scheduled to last 23 days. Since enrollment is done continuously, activities of D0 will start on the 8th day after screening and activities of D1 on the 9th day and run concurrently with the screening.

Two teams will be required during the screening period, one to do the baseline screening to identify eligible children for the clinical trial. The other (composed of at least one physician) will examine children for inclusion and exclusion criteria, recruit and treat them with PZQ on D0 and assess them for adverse drug events 4 hours after treatment on D0, on D1 and D21. In addition, on D21 cure rate and egg reduction rate will be determined. At six months (6M) and 12 months (12M) after treatment, trial subjects in the two groups will be followed up for determination of cure rate, egg reduction rate, weight and Hb. Here is a detailed account of the activities to be undertaken at D0, D1, D21, 6M and 12M, their timings (with ranges) and the assessments to be made.

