### 3.3. Randomization:

Schoolchildren with *S. mansoni* and fulfilling both inclusion and exclusion criteria will be randomly assigned to two groups: one group will receive PZQ 40mg/kg and the other group PZQ 60mg/kg. Randomization will be generated in blocks of 4, in a ratio of 1:1 for each drug regimen. Sealed and numbered envelopes containing the treatment regimen for each sequential participant to be enrolled will be provided from TDR. The envelopes containing the codes will be kept in a locked cabinet and one designated person of the team will be responsible for them. This same person will be responsible for opening the envelope and verifying the corresponding treatment once a new participant is enrolled in the study. Each participant will be assigned a unique Study I.D. number (ID#). This ID# will be assigned in sequential order and will be recorded in the Screening Log. The treatment will be provided to the participant according to the Praziquantel regimen assigned by the randomization code and the participant's weight (Appendix 6). An electronic, password-protected copy of the randomization codes will be kept at TDR, Geneva.

The opened envelopes will be signed, dated, resealed and kept in the locked cabinet.

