### 3.4. Blinding:

Blinding of the study will be achieved by ensuring that the person who calculates the dosage of PZQ to be given and provides the medication to the participants is not the person who evaluates safety. In addition those doing the parasitological analysis will not know the treatment given to the individual children.

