## APPENDIX 2.

Table 1. Number of praziquantel tablets to be given to subjects under the 40mg/kg and 60mg/kg regimens.

| 40 mg/kg regimen |                   | 60 mg/kg regimen |                   |
|------------------|-------------------|------------------|-------------------|
| Bodyweight (kg)  | Number of tablets | Bodyweight (kg)  | Number of tablets |
| 13-15            | 1                 | 10               | 1                 |
| 16-18            | 1 ¼               | 10 - 12.5        | 1 ¼               |
| 19 – 22          | 1 ½               | 12.6 - 15        | 1 ½               |
| 23 – 25          | 1 ¾               | 15 - 17.5        | 1 ¾               |
| 26 – 29          | 2                 | 17.6 - 20        | 2                 |
| 30 – 33          | 2 ¼               | 20 - 22.5        | 2 ¼               |
| 34 – 37          | 2 ½               | 22.6 - 25        | 2 ½               |
| 38 – 40          | 2 ¾               | 25 - 27.5        | 2 ¾               |
| 41 – 44          | 3                 | 27.6 - 30        | 3                 |
| 45 – 48          | 3 ¼               | 30 - 32.5        | 3 ¼               |
| 49 – 52          | 3 ½               | 32.6 - 35        | 3 ½               |
| 53 – 55          | 3 ¾               | 35 - 37.5        | 3 ¾               |
| 56 – 59          | 4                 | 37.6 - 40        | 4                 |
| 60 – 63          | 4 ¼               | 40 - 42.5        | 4 ¼               |
| 64 – 66          | 4 ½               | 42.6 - 45        | 4 ½               |
| 67 – 70          | 4 ¾               | 45 - 47.5        | 4 ¾               |
| 71 – 75          | 5                 | 47.6 - 50        | 5                 |
|                  |                   | 50 - 52.5        | 5 ¼               |
|                  |                   | 52.6 - 55        | 5 ½               |
|                  |                   | 55 - 57.5        | 5 ¾               |
|                  |                   | 57.6 - 60        | 6                 |

In this table, 13-15 means 13.1 kg to 15.9 kg. The same applies to the other weight ranges

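### The protocol calls the trial double-blind, but masks only the safety evaluator and the slide readers; the symptom comparison is not participant-blind, and printed fixed blocks of 4 leave a residual, conditional route to selection

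*Protocol*

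**What the plan says.** Section 3.2 gives the label: "The proposed study is a double-blind, randomized controlled trial". Section 3.4 then describes how blinding is achieved, and contains two measures. The person who calculates the dose and "provides the medication to the participants is not the person who evaluates safety", and "those doing the parasitological analysis will not know the treatment given to the individual children".

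Appendix 2 is a table of the "Number of praziquantel tablets to be given to subjects under the 40mg/kg and 60mg/kg regimens". The two regimens have separate columns, and there is no placebo column. Section 5.1 has the medication given under direct observation and describes no masking of the tablets.

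Section 3.2 also describes the two field teams. The second one, which includes at least one physician, is to examine children against the criteria, "recruit and treat them with PZQ on D0 and assess them for adverse drug events 4 hours after treatment".

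Section 3.3 states: "Randomization will be generated in blocks of 4, in a ratio of 1:1 for each drug regimen". Envelopes are sealed, numbered and kept locked. One designated team member opens each of them once a child is enrolled.

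**The concern.** A double-blind label is normally read to mean that participants as well as assessors do not know the assignment. Here both stated measures concern observers. The child swallows a number of tablets that depends on the arm, and a few hours later answers a symptom questionnaire. The main objective (section 2) requires an adequate safety profile as well as better efficacy. The adverse-event comparison (secondary endpoint b) is therefore part of what the trial is meant to show. If it is reported as double-blind, readers will give the symptom items more weight than the design supports.

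A second, separate matter is allocation. With a known fixed block size, past assignments carry information about the next one. If anyone who decides on eligibility also knows what was given before, enrolment is open to selection. That would affect every endpoint, including the primary one.

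**Working it through.** The protocol gives no figure for blinding or predictability, so there is none to reproduce. The total of 236 (2 × 118, section 5, Table 2) is taken as stated.

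**1. Who is masked**

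| Party | Measure described | Where |
|---|---|---|
| Safety evaluator | Not the person who doses | 3.4 |
| Slide readers | Do not know the treatment | 3.4 |
| Child | None | 3.4, 5, 5.1, Appendix 2 |
| Staff deciding eligibility | None stated | 3.2, 3.3, 3.4 |

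**2. What the child can see** (Appendix 2, same body weight)

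| Weight | 40 mg/kg arm | 60 mg/kg arm | Difference |
|---|---|---|---|
| 28 kg | 2 | 3 | 1 |
| 39 kg | 2¾ | 4 | 1¼ |
| 58 kg | 4 | 6 | 2 |

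The counts overlap across weights. Three tablets is the entry for 41–44 kg in one column and for 27.6–30 kg in the other. A count alone therefore does not always identify the arm. A count together with the weight and the table does, and two children of similar size can compare. There is opportunity to do so. Appendix 1 has eight dosing days, so about 236 / 8 = 29.5 children are dosed per day, and section 8.2 keeps them at the school for at least 4 hours, with the first questionnaire at 4 hours.

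**3. Which results depend on the child's knowledge**

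- Section 8.2 lists nine items. Five rest essentially on the child's account: abdominal pain, nausea, anorexia, headache and dizziness. Four have observable signs: vomiting, diarrhoea, fever and allergic reaction.
- Cure rate and egg counts come from slides read without knowledge of treatment (3.4).
- Haemoglobin and weight come from digital instruments (6.2.4, 6.2.5).

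**4. How much a fixed block of 4 can reveal**

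There are 6 equally likely orders of two A and two B. Assume an observer who knows every earlier assignment and where each block starts.

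- Positions 1 and 2 are never certain.
- Position 3 is certain only if the first two were alike: 2 of 6 orders, or 1/3.
- Position 4 is always certain.
- Certain per block: 1/3 + 1 = 1.33 of 4, or 33.3%.
- Over the trial: 236 / 4 = 59 blocks, and 59 × 1.333 = 78.7, about 79 assignments on average.
- Best guess correct: 1/2 + 2/3 + 2/3 + 1 = 2.83 of 4, or 70.8%, against 50% without the information.

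**5. Whether such an observer exists**

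The envelope holder knows past assignments and belongs to the team. Section 3.3 does not say which of the two field teams, and nothing bars that person or the dispenser from eligibility decisions. Some Day 0 criteria need judgement, namely physical fitness to take part (section 3.2, D0) and clinical malaria by symptoms such as headache or malaise (6.1.1).

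**The case against.** The strongest reply is that the protocol protects more than the label dispute suggests, and much of that stands.

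- A reader of the two-team paragraph might infer that the same person treats and assesses. Section 3.4 rules this out: the dispenser may not evaluate safety, and the Day 1 and Day 21 assessments are given to the physician. The paragraph describes a team with several roles. What remains is that the two places should be worded consistently.
- A reader might infer that children know their arm. The documents do not show this. Nothing says that children see the dosing table, and the counts overlap across weights. What is supported is that no measure prevents a child from finding out.
- A reader might infer that a third of the allocation is predictable in practice. Envelopes are sealed, locked, opened only after enrolment, then resealed. No passage says that recruiters watch dosing or learn past codes. The main entry criterion, the egg count, is a mean of four screening slides and leaves no discretion. Fixed blocks of 4 with sealed envelopes are not in themselves an error.
- Safety is not all self-report. Children are observed for at least 4 hours, fever and vomiting have graded signs, and Day 21 haemoglobin is also a safety measure.

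None of this supplies masking of the child, and none of it keeps the envelope holder or dispenser away from eligibility decisions.

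**Conclusion.** The label in section 3.2 is not supported by section 3.4 and should be corrected. This rests on the text alone. The reach is limited to the self-reported symptom items of secondary endpoint b, five of the nine listed. The documents give no ground for saying that masking fails for the primary cure rate or for the egg counts. The direction and size of any reporting bias cannot be derived from the protocol.

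The allocation point is weaker and conditional. The 33.3% (about 79 of 236) assumes full knowledge of earlier assignments and block boundaries, so it is an upper bound on what a partly informed recruiter could know for certain. It shows a route that is open, and is no evidence that anyone would use it. Both points merit a change before the start because the changes are small and affect what the trial may claim.

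**What to change.** 1. In sections 3.2 and 3.4, describe the trial as assessor-blind, naming the safety evaluator and the microscopists, and state that the symptom comparison is not participant-blind. If masking of the child is in fact intended, section 3.4 should say how it is done.
2. State that dosing takes place out of sight of assessors, recruiters and other children. Direct observation by the designated dispenser can stay as it is.
3. Align the two-team paragraph in section 3.2 with section 3.4, so that the separation of dispenser and safety evaluator is plain in both. Add that the envelope holder and the dispenser take no part in eligibility decisions.
4. Have TDR, which already supplies the envelopes and holds the codes, generate the list with randomly varying block sizes that are not disclosed to the site. Replace the block size in section 3.3 with a statement to that effect.

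The cost is a weaker blinding label, a screened dosing point, and a new list and envelopes before the start. No placebo, extra participants or change of regimen is needed. Relabelling does not remove any reporting bias; it only states the standing of the comparison correctly.

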#### D0 (means 7 days after baseline study +/-1 day)

Clinical history of each schoolchild fulfilling screening criteria using questionnaire will be taken to see if the subject has acute or chronic severe disease, including hepato-splenic schistosomiasis. In addition, the questionnaire will seek to establish a history of adverse reactions associated with PZQ, a history of treatment with PZQ within 30 days and medication (such as antibiotics) currently being used which may affect the results of the present trial. This will be followed by a thorough physical examination by a physician for physical fitness to participate in the trial. Those showing signs and symptoms of clinical malaria will be referred for treatment and excluded from the study and referred for treatment. Childbearing age female subjects will further be tested for pregnancy using the Quickstick™ One step HCG Pregnancy Test. Those tested positive for pregnancy will be excluded from the study. Each girl will be given individual counseling from the study nurse. Those children with schistosomiasis who will be excluded from the study at this point will be treated with a single oral dose of PZQ at 40mg/kg.

For the children who fulfill all criteria for enrolment, body weight will be determined and a finger-prick blood sample will be collected for Hb measurement. Thereafter they will be treated with PZQ according to weight and dosage regimen assigned in the trial (see randomization and blinding section for treatment assignment). During the 4 hours post-treatment study subjects will be observed for occurrence of adverse events and by the end of this period they will be assessed for adverse events using a questionnaire.

